To accurately identify key regulatory factors, cross-omics integrated screening of proteomic, metabolomic, transcriptomic, and microecological data will first be performed, using gene function or metabolic pathways as core dimensions to extract overlapping or strongly correlated modules of differential molecules across omics. This process will eliminate functionally irrelevant redundant information, ultimately selecting core differential markers that are co-occurring across multiple omics and closely associated with prognostic phenotypes (e.g., survival/death). Data preprocessing will be required prior to model construction: the screened core marker data will be integrated, Z-score standardization will be applied to eliminate dimensional discrepancies across different omics platforms, and the dataset will be randomly partitioned into a training set (for model development) and a test set (for preliminary validation) at a ratio of 8:2 to mitigate overfitting risks at the data level. In this process, samples from eight centers will be selected as training dataset according to the final number of enrolled patients, while the other two centers will act as validation set. The feature dimensionality reduction stage will employ a combined “unsupervised + supervised” strategy: unsupervised dimensionality reduction will first be conducted via principal component analysis (PCA), retaining principal components with a cumulative variance contribution rate > 80% to initially compress feature dimensions; subsequently, least absolute shrinkage and selection oerator (LASSO) will be applied for supervised dimensionality reduction, selecting features with non-zero coefficients to exclude irrelevant variables. For advanced applications, principal component regression (PCR) or partial least squares discriminant analysis (PLS-DA) will be integrated to further prioritize core features strongly correlated with prognostic phenotypes, ultimately refining high-dimensional features to 20–50 variables to balance model complexity and predictive performance. For model construction, appropriate multi-omics fusion strategies will be selected. For early fusion, all core omics features will be integrated first, followed by building a unified predictive model using algorithms such as random forest (RF) or support vector machine (SVM). For late fusion, individual predictive models will be constructed for each omics separately, and the results will then be integrated via weighted voting (e.g., transcriptomics model weight = 0.4, metabolomics = 0.3, proteomics = 0.3) or the Stacking ensemble method to improve prediction stability. Common tools to be utilized include the multi-omics prediction module in MetaboAnalyst and ensemble learning libraries within Python’s scikit-learn. Model performance will be rigorously evaluated using standardized metrics: classification models (e.g., survival/death prognostic prediction) will be quantified using accuracy, sensitivity, specificity, area under the ROC curve (AUC), and confusion matrix. Regression models (e.g., prognostic risk score prediction) will assess fitting efficacy using coefficient of determination (R²), root mean square error (RMSE), and mean absolute error (MAE). Notably, AUC ≥ 0.85 (for classification models) and R² ≥ 0.7 (for regression models) will be established as key criteria for confirming the clinical utility of the model.

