### Sample size calculation

The study hypothesizes that the developed model will achieve an area under the ROC curve of at least 0.85 for predicting the 28-day mortality in ARDS patients, and the goal is to test if this value is greater than 0.70, which is considered the threshold for good discriminant ability. The study is designed with α = 0.05 and β = 0.10, and the proportion of lost follow-up or withdrawal is less than 10%. The sample size was calculated using PASS-16 software, which determined that at least 66 deaths must be observed for the study. Referring to previous literature, the 28-day mortality rate of ARDS patients is about 40% [4,7,8], and it is estimated that 165 patients with ARDS need to be enrolled in the study. In addition, given the stringent quality requirements of multi-omics testing for samples and to account for potential test failure rates, we aim to enroll 200 patients to ensure the final testing meets the predetermined sample size requirements.

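### The utility bar for the model, an observed AUC of at least 0.85, equals the AUC assumed in planning, so the 90% power does not cover it and a model with a true AUC of exactly 0.85 misses it about half the time

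*Protocol article*

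**What the plan says.** Two places in the protocol article attach a number to the AUC of the 28-day mortality model.

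- **Sample size calculation.** "The study hypothesizes that the developed model will achieve an area under the ROC curve of at least 0.85", and "the goal is to test if this value is greater than 0.70, which is considered the threshold for good discriminant ability". With α = 0.05 and β = 0.10 this leads to 66 deaths. At about 40% mortality that becomes 165 patients, with 200 as the enrolment target.
- **Multi-Omics data analysis and integration.** Classification models "will be quantified using accuracy, sensitivity, specificity, area under the ROC curve (AUC), and confusion matrix". The section then states: "Notably, AUC ≥ 0.85 (for classification models", adds R² ≥ 0.7 for regression models, and says that these "will be established as key criteria for confirming the clinical utility of the model".

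The second place gives no confidence limit or margin for the 0.85. It does not say whether the AUC is the one from the training set, the test set (20% of the data) or the whole cohort. Neither place refers to the other.

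**The concern.** The value 0.85 does two jobs. It is the alternative on which the study was sized, and it is the bar that the observed AUC must reach for utility to be confirmed. The value the study is powered to exceed is 0.70.

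A cut-off placed at the assumed true value is passed about half the time. More patients narrow the spread around 0.85 but do not move its centre, so sample size does not help. A reader who sees 90% power beside a utility criterion of 0.85 may believe that a model as good as planned has a 90% chance of being confirmed as useful. Its chance is close to one in two.

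With two unreconciled thresholds, it is also open after the results are known which of them carries the conclusion.

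**Working it through.** **Inputs from the document.** Null AUC 0.70, planning AUC 0.85, α = 0.05 (sidedness not stated), power 0.90, 66 deaths, 40% mortality (66 deaths and 99 survivors among 165; 80 and 120 among 200), loss below 10%, test share 20%. **Assumption:** a 20% hold-out holds about 13 deaths and 20 survivors (of 165) or 16 and 24 (of 200).

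**1. The plan's own figure.** The binormal variance is V(A) = 0.0099·exp(−a²/2)·[(5a² + 8) + (a² + 8)/R], with a = 1.414·Φ⁻¹(A) and R survivors per death. For R = 1, V(0.70) = 0.1451 and V(0.85) = 0.0977. Deaths needed, two-sided:

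(1.96·√0.1451 + 1.2816·√0.0977)² / 0.15² = 1.316 / 0.0225 = 58.5, so 59.

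Then 59/0.90 = 65.6, so 66, and 66/0.40 = 165. The stated figures reproduce. This variant was found by search, because the document gives neither the sidedness nor the ratio. With R = 1.5, which 40% mortality implies, 37 to 51 deaths suffice before losses, depending on the variance formula and sidedness. So 66 is not too few for the test against 0.70.

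**2. Standard error.** Hanley-McNeil, with m deaths and n survivors:

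SE² = [A(1−A) + (m−1)(B₁−A²) + (n−1)(B₂−A²)] / (mn), where B₁ = A/(2−A) and B₂ = 2A²/(1+A).

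At A = 0.85, B₁ = 0.7391, B₂ = 0.7811 and A² = 0.7225.

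- 66/99: (0.1275 + 1.0810 + 5.7409)/6534 gives SE = 0.033.
- 13/20: (0.1275 + 0.1996 + 1.1130)/260 gives SE = 0.074.

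**3. The powered test, full cohort (66/99).** At A = 0.70 the SE is 0.0426. The test succeeds from an observed AUC of 0.70 + 1.645 × 0.0426 = 0.770 (one-sided) or 0.70 + 1.96 × 0.0426 = 0.783 (two-sided). At a true AUC of 0.85 it succeeds with probability Φ((0.85 − 0.770)/0.0326) = 99.3% or Φ((0.85 − 0.783)/0.0326) = 97.9%.

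**4. The 0.85 bar.** By normal approximation, P(observed ≥ 0.85 | true 0.85) = 1 − Φ(0) = 50% for any m and n. Simulating the empirical AUC under equal-variance binormal scores, 20,000 runs per case:

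| Deaths/survivors | True 0.70 | True 0.80 | True 0.85 | True 0.88 | True 0.90 |
|---|---|---|---|---|---|
| 66/99 | 0% | 7% | 52% | 87% | 98% |
| 80/120 | 0% | 5% | 52% | 89% | 98% |
| 13/20 | 5% | 29% | 55% | 72% | 84% |
| 16/24 | 3% | 25% | 53% | 73% | 84% |

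At a true AUC of 0.85 the bar is missed 48.4% (66/99), 48.0% (80/120), 45.1% (13/20) and 47.1% (16/24) of the time. A 90% pass chance needs a true AUC between 0.88 and 0.89 on the full 165, and above 0.90 in either hold-out.

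**5. Would a lower-limit rule help?** The rule is: observed AUC − 1.96·SE > 0.70, with the SE taken at the observed AUC.

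- 66/99: met from about 0.776 (0.765 with a one-sided limit), far below 0.85.
- 13/20: met from about 0.847. The AUC moves in steps of 1/260 here; 220/260 = 0.846 fails and 221/260 = 0.850 passes. The two rules therefore coincide: 55%, 29%, 13% and 5% at true AUC 0.85, 0.80, 0.75 and 0.70. A one-sided limit gives 64% at 0.85.
- 16/24: 61% at a true AUC of 0.85 (71% one-sided).

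The lower-limit rule restores the power only when the AUC rests on about the whole cohort.

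**The case against.** **A stricter second tier is legitimate.** The 0.70 test concerns discrimination and the 0.85 bar concerns clinical utility. Meeting the first and missing the second is then no contradiction. This stands as a possible design, but the text does not say that it is the design. Even so read, the stated power would not apply to the second tier.

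**The text does not say that a model is rejected.** A reader might infer that a model below 0.85 is discarded or declared a failure. The document speaks only of key criteria for confirming utility, names no consequence of missing them, calls the test set preliminary and calls the study exploratory. What can be said is that utility would not be confirmed.

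**The hypothesis is at least 0.85.** A better model passes more often, 98% at a true AUC of 0.90 on the full cohort. The one-half figure belongs to a true AUC of exactly 0.85, which is the value used for the power.

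**The models may differ.** The statistical analysis section builds a Cox model, while the multi-omics section describes random forest, support vector machine or stacked models. That leaves it less clear which claim the power supports.

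**Intervals may be in a fuller plan.** Possibly, and their absence from an article is not the point here. The point is that the stated bar coincides with the planning value.

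**Results between 0.78 and 0.849.** A reader might infer that any such AUC succeeds in one section and fails in the other. That holds only for an honest AUC over about the full cohort. In a 13/20 hold-out with a two-sided limit the band vanishes.

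**Conclusion.** The point holds in a limited form. The power claim and the utility rule use different thresholds, and the utility threshold equals the planning value. At a true AUC of exactly 0.85, utility goes unconfirmed about 48% of the time with 66/99 and about 45% to 47% in a 20% hold-out. The test that was powered succeeds 98% to 99% of the time on the full 66/99.

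These figures assume binormal scores, 40% mortality, the hold-out sizes above and an AUC free of optimism. An AUC computed on training data would be inflated and pass more often.

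Two stronger readings are not supported. The sample size is not shown to be too small for the test against 0.70. Nor is the 0.85 bar the sole cause of weak models passing by chance in a small test set: at 13/20 the lower-limit rule passes them equally often, because the cause there is the size of the test set.

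**What to change.** In the multi-omics section, base the confirmatory conclusion on the test the study was sized for: the lower 95% confidence limit of the AUC above 0.70. Compute it from out-of-sample predictions over the whole cohort, for example by cross-validation or by leaving out one centre at a time, with all feature selection repeated inside each fold. Always report the AUC with its interval, and state the sidedness. Do not apply the rule to a 20% hold-out alone and quote the 90% power for it.

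If 0.85 is kept, describe it as a separate, stricter utility benchmark and name the data set on which it is judged. State that the 90% power does not apply to it and that its chance of being met at a true AUC of 0.85 is about 50%.

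Either change should be made before outcome results are seen. The cost is a few sentences, a little more computation and a criterion that sounds less ambitious. No additional patients are needed.

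### The study is powered to show an AUC above 0.70, but success is judged by AUC ≥ 0.85, the planning value itself, so the stated 90% power does not apply to that criterion

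*Protocol article*

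**What the plan says.** The Sample size calculation section supposes that "the developed model will achieve an area under the ROC curve of at least 0.85 for predicting the 28-day mortality in ARDS patients", and adds that "the goal is to test if this value is greater than 0.70". It sets α = 0.05, β = 0.10 and loss below 10%, and concludes that "at least 66 deaths must be observed for the study". With 28-day mortality of about 40%, "it is estimated that 165 patients with ARDS need to be enrolled in the study". To allow for failed assays, "we aim to enroll 200 patients to ensure the final testing meets the predetermined sample size requirements".

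The Multi-Omics data analysis and integration section evaluates the models and closes with the bar for clinical utility: "AUC ≥ 0.85 (for classification models) and R² ≥ 0.7 (for regression models) will be established as key criteria". It gives AUC as a metric for classification models, with survival or death as the example. It gives R² as a metric for regression models, with a prognostic risk score as the example. No interval or test accompanies either threshold, and the value 0.70 for the AUC does not appear there. The same section plans an 8:2 division into training and test data.

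**The concern.** The two sections use 0.85 in different roles. In the sample size calculation it is the assumed true value, and 0.70 is the value to be beaten. In the analysis section 0.85 is the value that the result must reach. An estimate falls below its own true value about half the time, so a pass mark set at the assumed truth cannot be met with 90% probability, and recruiting more patients does not change that.

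The study's main conclusion is at stake. A result that rejects an AUC of 0.70, which is what the study was sized to do, could be reported as a success under one section and as failing to confirm utility under the other. The document does not say how such a result is to be read.

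**Working it through.** **Inputs.** Planned AUC 0.85, null AUC 0.70, α = 0.05, power 0.90, loss up to 10%, 66 deaths, mortality 40%, 165 patients and a target of 200 (Sample size calculation). A 20% test share (Multi-Omics data analysis and integration). The sidedness of α is not stated; two-sided is assumed because it reproduces the plan's figure.

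**1. The plan's own figure.** The binormal variance for one ROC curve is V(A) = exp(−a²/2)/(32π) × [(5a² + 8) + (a² + 8)/R], where a = √2·z(A) and R is survivors per death.

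With R = 1, V(0.70) = 0.1458 and V(0.85) = 0.0982. Deaths = [(1.960·√0.1458 + 1.282·√0.0982)/0.15]² = 58.8, so 59. Then 59/0.90 = 65.6, so 66, and 66/0.40 = 165. Both published figures reproduce, and they belong to the test against 0.70.

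**2. Where the powered test succeeds.** With 66 deaths and 99 survivors, R = 1.5, V(0.70) = 0.1243 and V(0.85) = 0.0867. The standard errors are √(0.1243/66) = 0.0434 and √(0.0867/66) = 0.0362. The estimate must exceed 0.70 + 1.96 × 0.0434 = 0.785. Power at a true AUC of 0.85 is Φ[(0.85 − 0.785)/0.0362], about 0.96. With 59 deaths and 89 survivors (10% lost), the boundary is 0.790 and the power about 0.94.

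**3. The stated criterion.** By the normal approximation, P(estimate ≥ 0.85) = Φ[(A − 0.85)/SE(A)]. At A = 0.85 this is Φ(0) = 0.50 for every sample size. Binormal simulation of the empirical AUC (20,000 runs per setting) gives slightly more, because the estimate is skewed:

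| Deaths/survivors | Basis | P(AUC ≥ 0.85), true AUC 0.85 |
|---|---|---|
| 66/99 | 165 patients | 0.52 |
| 59/89 | 165 less 10% | 0.52 |
| 80/120 | 200 patients | 0.51 |
| 16/24 | 20% of 200 | 0.53 |
| 13/20 | 20% of 165 | 0.55 |

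At 66/99 the rule passes a true AUC of 0.80 about 7% of the time and a true AUC of 0.90 about 97%. By the normal approximation, a 90% pass probability needs a true AUC of about 0.89 at 66/99, or 0.92 to 0.93 in a 20% test set.

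**4. How often the two rules part.** At 66/99 with a true AUC of 0.85, about 47% of simulated studies have a DeLong lower 95% limit above 0.70 and an estimate below 0.85. At a true AUC of 0.80 the figure is about 72%.

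**5. The powered rule in a 20% test set.** Requiring the DeLong lower limit to exceed 0.70 passes a true AUC of 0.85 about 99% of the time at 66/99, but only about 58% at 13/20 and 64% at 16/24. The planning formula is harsher in the small sets, at about 31% and 38%. The power claim therefore needs about 66 deaths to contribute to the validated AUC.

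**The case against.** The best defence is that the two sections ask different questions. One tests discrimination against 0.70; the other sets a bar for clinical utility, which may properly be higher than a statistical null. On that reading, an AUC of 0.82 with an interval above 0.70 is no contradiction: discrimination is shown and the higher bar is missed. The planning text also says at least 0.85, so a better model fails less often. The limitations paragraph of the Discussion calls the study exploratory, and the test set is described as preliminary validation.

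Much of this stands. A stricter bar could be deliberate, and the one-half figure holds only at a true AUC of exactly 0.85. But the document does not say that the bar is separate, does not give its pass probability, and uses the same number as planning value and threshold.

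Four stronger readings are tempting and not supported:

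- That R² ≥ 0.7 contradicts AUC ≥ 0.85. The text applies R² to regression models and never to binary 28-day death. Any conversion between the two needs an assumption that the document does not make. What can be said is that R² has no hypothesis, expected value or sizing.
- That the 0.85 rule is specially prone to pass weak models in a small test set. At 13/20 it passes a true AUC of 0.75 about 13% of the time, and the lower-limit rule about 15%. The document also does not say on which data the criterion is judged.
- That the lack of calibration or net-benefit measures is part of the error. An article may leave these to the full protocol or analysis plan.
- That the sample size is wrong. It reproduces.

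**Conclusion.** The concern holds for the AUC. The stated 90% power attaches to the test against 0.70, not to the criterion of 0.85. A model exactly as good as planned meets that criterion about 50–55% of the time at every planned size and so misses it in 45–50% of studies, against the 10% that β = 0.10 implies. Estimates from about 0.79 to 0.85 at 66/99 fall between the two rules.

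This rests on three assumptions: the criterion is read as a point estimate, because no interval is mentioned; scores are equal-variance binormal; and mortality is 40%. If the lower confidence limit had to reach 0.85, the planned model would fail nearly always, so the first assumption does not favour the finding. The one-half result depends little on the other two.

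**What to change.** State one success rule in both sections: the lower limit of the two-sided 95% confidence interval of the validated AUC exceeds 0.70. Judge it on cross-validated or resampled predictions for all patients, with feature selection repeated inside each resample, so that about 66 deaths contribute. A 20% test set with 13–16 deaths would leave only about 58–64% power and could be reported as a secondary result. Keep 0.85 as the planning value.

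If 0.85 is meant as a separate, stricter utility bar, say so, and state that its pass probability is about 50% when the true AUC is 0.85.

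Add one sentence saying that R² ≥ 0.7 has no hypothesis or sizing behind it and does not apply to binary 28-day death. Calibration and net benefit may be added but are optional here.

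The cost is a paragraph of wording and some computing. No new data or patients are needed, but the wording should be settled before the outcome analysis.

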
### Outcomes

The primary outcome of this study is the 28-day clinical outcome, which includes survival and death. The secondary outcomes include 28-day ICU length of stay and ventilator-free days. For patients with moderate to severe ARDS undergoing invasive mechanical ventilation, additional outcomes include RNA-seq, and scRNA-seq analyses of peripheral blood and BALF will be collected on 24h of inclusion and before extubation. For patients unable to be extubated within 7–14 days, samples will be collected during this period. Respiratory mechanics parameters, severe ultrasound indexes, EIT data, the correlation of physiological parameters will also be evaluated using binary analysis.

### Sample size calculation

The study hypothesizes that the developed model will achieve an area under the ROC curve of at least 0.85 for predicting the 28-day mortality in ARDS patients, and the goal is to test if this value is greater than 0.70, which is considered the threshold for good discriminant ability. The study is designed with α = 0.05 and β = 0.10, and the proportion of lost follow-up or withdrawal is less than 10%. The sample size was calculated using PASS-16 software, which determined that at least 66 deaths must be observed for the study. Referring to previous literature, the 28-day mortality rate of ARDS patients is about 40% [4,7,8], and it is estimated that 165 patients with ARDS need to be enrolled in the study. In addition, given the stringent quality requirements of multi-omics testing for samples and to account for potential test failure rates, we aim to enroll 200 patients to ensure the final testing meets the predetermined sample size requirements.

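### The stated 90% power assumes a fixed model tested on the whole cohort; on the planned 20% hold-out it is about 30–38% two-sided, and the protocol does not say which data carry the test

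*Protocol article*

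**What the plan says.** The Sample size calculation section of the protocol article hypothesises that "the developed model will achieve an area under the ROC curve of at least 0.85 for predicting the 28-day mortality in ARDS patients", and says that "the goal is to test if this value is greater than 0.70". It continues: "The study is designed with α = 0.05 and β = 0.10", and adds that "the proportion of lost follow-up or withdrawal is less than 10" per cent. PASS-16 was used, "which determined that at least 66 deaths must be observed for the study". With the assumption that "the 28-day mortality rate of ARDS patients is about 40" per cent, "it is estimated that 165 patients with ARDS need to be enrolled in the study". Enrolment is then raised to 200 to cover assay failures. The section does not mention a split of the data.

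The section on multi-omics data analysis and integration describes how the model is built. The data are "randomly partitioned into a training set (for model development) and a test set (for preliminary validation) at a ratio of 8:2". The same paragraph then says that eight centres form the training data and the other two the validation set, chosen according to final enrolment. It makes an AUC of at least 0.85 a key criterion of clinical utility.

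The Statistical analysis section evaluates a Cox model for 28-day mortality by AUC, again without naming a data set. The Discussion calls the study exploratory and concedes that the sample is limited for high-dimensional work.

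**The concern.** A one-sample ROC power calculation applies to a marker or model that is fixed before it meets the patients on whom it is tested. The 66 deaths are every death expected in the cohort of 165, yet about four fifths of those patients will be used to screen markers, reduce dimensions, select features and fit the model. The stated power therefore does not belong to the evaluation that the plan describes.

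Two readings are open, because the plan does not name the data set for the test against 0.70:

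- **Hold-out.** The test rests on about 13 to 16 deaths, not 66.
- **Whole cohort.** The AUC is computed largely on patients who shaped the model. It is biased upwards, and a calculation for a fixed model does not apply.

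At stake is the study's main quantitative promise. Under the first reading, a good model has a substantial chance of not being shown better than 0.70. Under the second, a poor model could appear to pass.

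**Working it through.** **Inputs.** From the Sample size calculation: AUC 0.85 against 0.70, alpha 0.05 (sidedness not stated), beta 0.10, loss below 10% (10% used), mortality 40%, 66 deaths, 165 patients, target 200. From the multi-omics section: an 8:2 split.

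**Step 1: reproduce the plan's figure.** Let R be survivors per death. The required deaths are

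n = [z(alpha) √V(0.70) + z(beta) √V(0.85)]² / 0.15²

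with the Obuchowski variance V = 0.0099 exp(−a²/2) [(5a² + 8) + (a² + 8)/R], where a = 1.414 z(AUC).

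- R = 1: V(0.70) = 0.1451 and V(0.85) = 0.0977.
- Two-sided: n = (1.960 × 0.3810 + 1.282 × 0.3126)² / 0.0225 = 58.5, so 59 deaths.
- 59/0.9 = 65.6, so 66. Then 66/0.40 = 165.

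Both figures match exactly. The match needs two choices that the article does not state: a two-sided test and one survivor per death. At the 40:60 mix implied by 40% mortality (R = 1.5) the same formula gives 50.5, so 51 deaths. The plan's choice is therefore conservative.

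**Step 2: size of a 20% hold-out.**

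- 0.2 × 165 = 33 patients; 0.4 × 33 = 13.2, so about 13 deaths and 20 survivors.
- 0.2 × 200 = 40 patients; 0.4 × 40 = 16 deaths and 24 survivors.

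**Step 3: power at a true AUC of 0.85.** With null variance, power = Φ{[0.15 − z(alpha) SE(0.70)] / SE(0.85)}. With alternative variance only, power = Φ{0.15/SE(0.85) − z(alpha)}. Three variances were used:

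- Obuchowski, as above, with SE = √(V/deaths).
- Hanley–McNeil: SE² = [A(1−A) + (n₁−1)(Q₁−A²) + (n₀−1)(Q₂−A²)]/(n₁n₀), Q₁ = A/(2−A), Q₂ = 2A²/(1+A), with n₁ deaths and n₀ survivors.
- Full binormal (Obuchowski–McClish, equal variances): V = f²(1 + 1/R)(1 + a²/8), a = √2 z(A), f = exp(−a²/4)/√(4π).

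| Deaths/survivors | Variance | SE(0.70) | SE(0.85) | Null variance: two-sided / one-sided | Alternative only: two-sided / one-sided |
|---|---|---|---|---|---|
| 13/20 | Hanley–McNeil | 0.0968 | 0.0744 | 30% / 45% | 52% / 64% |
| 13/20 | Obuchowski | 0.0971 | 0.0812 | 31% / 45% | 46% / 58% |
| 13/20 | Full binormal | 0.0906 | 0.0662 | 34% / 51% | 62% / 73% |
| 16/24 | Hanley–McNeil | 0.0873 | 0.0670 | 38% / 54% | 61% / 72% |
| 16/24 | Obuchowski | 0.0879 | 0.0734 | 38% / 53% | 53% / 65% |
| 16/24 | Full binormal | 0.0820 | 0.0599 | 43% / 60% | 71% / 80% |

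Example, Obuchowski at 13/20, two-sided: (0.15 − 1.960 × 0.0971)/0.0812 = −0.50, and Φ(−0.50) = 31%.

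For comparison, a fixed model tested on 66 deaths and 99 survivors would have 96% (Obuchowski) to 98% (Hanley–McNeil) two-sided power with null variance.

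A simulation of 4,000 data sets at 13/20 with DeLong intervals gave 34% two-sided on the logit scale and 57% with a Wald interval. The middle 95% of observed AUCs ran from about 0.69 to 0.97.

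**Step 4: precision at AUC 0.85 (Hanley–McNeil).** The 95% half-width is 1.96 × 0.0744 = 0.146 with 13/20 and 1.96 × 0.0670 = 0.131 with 16/24. With 66/99 it is 1.96 × 0.0326 = 0.064.

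**Step 5: what a powered hold-out would need.** By the formula that reproduces 66, at the 40:60 mix, the hold-out itself needs 51 deaths. That is 51/0.40 = 127.5 patients in the hold-out, and 127.5/0.2 = 637.5, about 640 patients in all under an 8:2 split.

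**The case against.** **The test against 0.70 is never placed in the hold-out.** This is correct. The test set is described as preliminary validation, and the criterion attached to the model is an AUC of at least 0.85, not superiority to 0.70. A reader might infer that the plan commits itself to a test with 30% power, and the text does not support that. It does not rescue the 90% either, because the alternative is to test on patients most of whom trained the model.

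**The size of the hold-out is not fixed.** Also correct. A random 8:2 split and an eight/two-centre split are different designs, and two centres may supply more or less than 20% of patients. The 13 and 16 deaths hold for a 20% share.

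**About 30% is the low end.** This stands. It assumes 165 patients, a two-sided test and null variance. The target is 200, and the aim is worded directionally. One-sided power at 16/24 is 53–54% by the two simpler formulas, so it would be wrong to say that a model with true AUC 0.85 would probably fail under every reading. Two-sided is, however, the reading that reproduces the plan's 66.

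**The Discussion admits that the sample is limited and asks for independent validation.** That softens the consequence but leaves the power statement uncorrected.

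**The 66 and 165 themselves.** Because 165 is exactly 66/0.40, a reader might infer that loss was forgotten, that 165/0.9 (184 patients) are needed, or that only 8.3% of the 200 remains for failed assays. The documents do not support this. On the derivation that matches, the 10% loss is already inside 66, and 165 × 0.9 × 0.4 = 59.4 deaths, which meets the 59 required. Taking off 10% again would count it twice, and the plan states no assay-failure rate.

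**Conclusion.** The point holds. The 90% power belongs to a fixed model tested on the whole cohort, and neither reading of the plan provides that. On a 20% hold-out, power with null variance is about 30–38% two-sided or 45–54% one-sided (Hanley–McNeil and Obuchowski). The full binormal variance and alternative-variance-only forms give more, up to 80% in the most favourable case, but none reaches 90%. An AUC of 0.85 would carry a 95% half-width of about 0.13–0.15. On the full cohort the AUC is optimistic and the calculation does not apply.

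These figures assume 40% mortality, a 20% hold-out share, no loss before the split, and a developed model whose true AUC is 0.85.

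The derivation of 66 and 165 is sound. Only the wording is loose: if 66 already includes the loss, about 59 deaths must be observed, not 66. That is a clarification and does not change the sample size.

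**What to change.** - In the Sample size calculation, say that the 90% power is for a fixed model on the full cohort and does not apply to the hold-out. Give the hold-out's own power and CI half-width, with sidedness and variance method.
- Name the data set and estimate on which the comparison with 0.70 is made.
- Make the primary performance estimate a cross-validated one that uses every patient, by nested or leave-one-centre-out cross-validation. Marker screening, scaling, feature selection and fitting should all be repeated inside each fold; the plan now describes screening and standardisation before the partition. Report a pooled AUC with a bootstrap confidence interval. Other resampling schemes could serve if they keep the whole pipeline inside.
- Choose between the random 8:2 and the eight/two-centre split, and label any single hold-out as descriptive.
- Wording only: state that 66 already includes the 10% loss, that about 59 deaths must be observed, and that the calculation was two-sided with one survivor per death (if the sponsor confirms this).

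Cost: changes to the text, more computing, and a less favourable stated power for the hold-out. No extra patients or samples are needed.
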